### Recruitment and randomization

Male and female participants will be recruited using advertisements on local media, newspapers, social media, official papers, and websites. We will also recruit from our existing database of participants and friends or relatives of the hospital and university staff. After approval and completion of the initial assessment, the subjects will be formally included in the study and randomized with a simple 1:1:1 randomization to the intervention arms through a web-based online randomization procedure. No adaptive randomization procedures will be performed. The random allocation sequence will be produced and managed by an investigator who will not take part in the participants’ recruitment. The order of assignments will be kept hidden from the investigators who will enroll participants or assign interventions. Group allocation will be presented on a folded paper in a sealed envelope.

### Blinding

In this trial, blinding of participants and dieticians is not possible because there are obvious differences between the intervention diets. However, outcome measures in the present study cannot be easily influenced by the observer. Trial personnel who will enroll participants, data collectors, outcome assessors, and data analysts will be blinded to treatment allocation, and an employee outside of the research team will input data into the computer on separate data sheets. On the other hand, making the trial open rather than blinded may improve recruitment.

### Data collection

Follow-up assessments and data collection will be undertaken by trial personnel at the Unit of Clinical Nutrition of the Careggi University Hospital in Florence, Italy. All subjects will be examined between 6:30 and 9:30 a.m. after a 12-h fasting period.

#### Compliance

Compliance with the intervention is critical to the success of this project and will be achieved using behavior change strategies including self-monitoring, and regular phone calls for dietary counseling. To ensure good compliance, participants will be given a detailed 1-week menu plan for each dietary period with all foods expressed in weight and/or volume measurements. Participants will be contacted at least twice during the study period to promote diet compliance. A dietician will make unannounced telephone calls, and each participant will recall his or her 24-h diet. Participants may discontinue the intervention or withdraw from the study for the following reasons: (1) at the request of the participant; (2) if the investigator considers that a participant’s health will be compromised due to adverse events or a concomitant illness that develops after entering the study. Participants prematurely discontinued from the study before the 3-month evaluation will have the baseline clinical and laboratory evaluations performed.

#### Anthropometric measurements and body composition

Weight and height will be measured using a stadiometer. Body mass index (BMI) will be calculated as weight (kilograms)/height (square meters). Body composition will be determined with a bioelectrical impedance analyzer device (Akern, model SE 101) at the baseline and follow-up visits.

#### Blood samples

Blood samples will be collected at the beginning and at the end of each intervention phase. Blood samples will be centrifuged at 3000 rpm for 15 min, aliquoted to yield serum, and then stored at − 80 °C until analyses. The following biochemical measurements will be evaluated: complete blood count, lipid profile (total cholesterol, LDL cholesterol, HDL cholesterol, triglycerides), fasting glucose, liver function tests (aspartate aminotransferase, alanine transaminase, gamma-glutamyl transferase), renal function tests (serum creatinine, urea, uric acid), mineral profile (sodium, potassium, magnesium, calcium), iron metabolism (iron, ferritin), vitamin profile (vitamin B_12_, folic acid), pro- and anti-inflammatory profile (hs-CRP), and circulating levels of inflammatory cytokines (IL-1ra, IL-1β, IL-2, IL-4, IL-6, IL-8, IL-10, IL-12, IL-17, IL-18, TNFα, IFNγ, VEGF, MCP-1, and IP-10)*.* All the cytokines will be determined with the Bio-Plex cytokine assay (Bio-Rad Laboratories Inc., Hercules, CA, USA), according to the manufacturer’s instructions.

#### Stool samples

Stool samples (four or five scoops totaling 4 g) will be collected before and after each intervention phase. Stool sample collection kits, including containers, will be provided for the participant. The following stool measurements will be evaluated: fecal microbiota profiles (bacteria and fungi), targeted metabolomic profiles (SCFAs, amino acids, and secondary bile acids such as deoxycholic acid), genotoxicity and cytotoxicity of fecal water (on normal and preneoplastic colon epithelial cells), mutagenicity of fecal water (yeast model), markers of global peroxidation of fecal water (heme, TBARs), and markers of specific peroxidation of omega-3 and omega-6 PUFAs in fecal water.

#### Storage of biological specimens

The storage of biological specimens will be performed under appropriate conditions, according to standard methods. Blood samples will be aliquoted and stored at − 20 °C for 4 years before being used or destroyed. The stored samples will be used exclusively for research purposes upon consent of the donor. The destruction of samples will be appropriately documented.

### Data management

Data will be collected on an electronic database. Identifiable data or other documents will not be recorded in the database, and participants will be identified by a unique trial ID only. Hard copies of data sheets linking the participants’ ID numbers to their contact details will be kept securely in a locked filing cabinet in a locked office, accessible only to key research team members. Participant files and other source data (including copies of protocols, questionnaires, original reports of test results, correspondence, records of informed consent, and other documents pertaining to the conduct of the study) will be kept for the maximum period of time permitted by the institution. All of the project data will be stored in the Data Sharing In Nutrition (DASH-IN) infrastructure, which is developed by the European Nutritional Phenotype Assessment and Data Sharing Initiative (ENPADASI). Thereby we will adhere to the FAIR principles (Findable, Accessible, Interoperable, and Reusable). The data will be made open access upon publication. Within Europe the ELIXIR infrastructure is coordinating data stewardship and management activities in the life sciences.

Multiple strategies will be employed to improve data quality during data collection, including an accurate recruitment, a structured and time-limited protocol, the inclusion of a run-in period, the limitation of the burden and inconvenience of data collection on the participants, the development of a trusting and collaborative relationship between research units and participants, and double data entry.

### Statistical analysis

Outcomes will be analyzed by intention-to-treat and on-treatment procedures. The primary outcome (fecal water genotoxicity) will be analyzed within each group using paired comparison *t* tests to evaluate whether the changes from baseline to 3 months will be statistically significant. The absolute change (mean value at baseline subtracted from the mean value after intervention for each subject) will be estimated with independent *t* sample tests. One-way analysis of variance will be used for testing differences between changes in the three diet groups. A general linear model for repeated measurements (after checking regression assumptions) will be performed in order to compare the effects of the three different treatments. A model with adjustments for multiple confounders will be used. Data for the general linear model will be reported as geometric means with their standard errors. Multiple strategies will be employed to reduce attrition, including an accurate recruitment, a structured and time-limited protocol, the inclusion of a run-in period, the limitation of the burden and inconvenience of data collection on the participants, and the development of a trusting and collaborative relationship between research units and participants. If a participant does not attend a scheduled appointment, a maximum of three telephone calls will be made and one email sent prior to withdrawing the participant from the study. If a participant wants to withdraw from the study intervention, the reason for withdrawal will be documented in the participant records for the subsequent analysis in the interpretation of the results.

Before starting the data analysis, the level, pattern, and likely causes of the missingness in the baseline variables and outcomes will be investigated by forming appropriate tables. This information will be used to determine whether the level and type of missing data have the potential to introduce bias into the analysis results or substantially reduce the precision of estimates for the proposed statistical methods. Sensitivity analyses will be undertaken, based on the assumption that missing outcomes are the worst possible, or the best possible, in different randomization groups. If these analyses show that conclusions may differ based on missing values, then supplementary multiple imputation for missing values will be undertaken. These analyses will account for results of any losses to follow-up insofar as they pertain to differences in measured variables (i.e., under the assumption of missing at random). A *p* value < 0.05 will be considered statistically significant. Statistical analyses will be performed using SPSS software for Macintosh (SPSS Inc., Chicago, IL, USA).

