The microbial fermentation of plant foods, associated with a low risk of CRC, increases intestinal short chain fatty acids (SCFAs), including butyrate, which has antineoplastic activity through its inhibition of histone deacetylase and the promotion of apoptosis [10], and also increases activated microbial phytochemicals, such as polyphenols with anti-inflammatory and antioxidant properties [11]. Consequently, it is known that diet influences the composition of the intestinal microbiome, as described by our group in a study on a rural human population [12], and the emerging evidence implies an involvement of the intestinal microbiota in CRC.

Cohort studies with subjects who consume various types of diets (e.g., omnivores, vegetarians, vegans) suggest that the diet alters the intestinal microbiome and the cytotoxic and genotoxic activities of the luminal colonic content [13]. However, although the association between the intestinal microbiota and the CRC is conceptually interesting, these results do not help to explain the mechanisms underlying the modulation of the intestinal microbiota by diet and the consequent impact on CRC risk.

We aimed to design this randomized, open, parallel clinical trial that will test whether diet effects on CRC risks are mediated by interaction with the intestinal microbiota and whether meat-based and pesco-vegetarian diets differentially modulate CRC risk biomarkers in clinically healthy subjects.

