### Outcome measures

#### Primary outcome

The primary outcome will be DNA damage (strand breaks and oxidized bases) in a human colon cancer cell line (HT29) exposed to fecal water. Genotoxic activity of fecal water will be determined by the comet assay, which evaluates the induction of DNA strand breaks and oxidized DNA bases upon exposure of the cells to fecal water [14]. The metric used will be changes in means from Time 0 to Time 1. Image acquisition will be performed with the Comet Assay IV software (Perceptive Instruments, UK). For each fecal water sample there will be a genotoxicity index (a single figure representing the mean area of the Comet tail [the percentage of DNA in the tail] measured in 100 cells). This figure will then be used in multivariate analyses to predict the potential operational taxonomy units (OTUs) measured using metagenomics approaches, potentially providing specific metabolic functions associated with the risk of neoplastic transformation [15, 16]. For this reason, this outcome was selected as the primary outcome of the study. In a previous study [14], fecal water activity markers were affected by specific dietary components linked with CRC risk such as red meat, and were sensitive to dietary supplementation with chemopreventive agents.

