### Sample size and power calculation

The sample size was determined to detect an anticipated change in fecal water-induced DNA damage evaluated through the comet assay of 25% from baseline, between the MBD and the PVD interventions. On the basis of a previously published trial conducted to test the efficacy of a dietary intervention on fecal water-induced DNA damage evaluated through the comet assay [14], a sample size of at least 50 in each group of the study will allow us to obtain a statistical power of 80% (beta) and alpha = 0.05, totaling 150 individuals. In case of loss to follow-up, extra volunteers will be enrolled to compensate. Losses will be included in the intention-to-treat but not in the per-protocol analyses.

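### The only tests tied by name to the primary outcome are within-diet paired t tests; several between-diet tests follow, but none is made decisive or linked to the powered MBD versus PVD contrast

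*Protocol article*

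**What the plan says.** All places are in the protocol article.

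- **Aim (Background).** The trial asks "whether meat-based and pesco-vegetarian diets differentially modulate CRC risk biomarkers in clinically healthy subjects". This is a question about a difference between diets.
- **Sample size and power calculation.** The trial is sized for a change "of 25% from baseline, between the MBD and the PVD interventions", with at least 50 per group, 80% power and alpha 0.05.
- **Primary outcome.** "The metric used will be changes in means from Time 0 to Time 1". No contrast between arms is given there.
- **Statistical analysis.** After a general statement that outcomes are analysed by intention to treat and on treatment, one sentence attaches a method to the primary outcome by name: "The primary outcome (fecal water genotoxicity) will be analyzed within each group using paired comparison" t tests, to see whether the 3-month change is significant. Three between-group methods follow. The absolute change "will be estimated with independent *t* sample tests", with no pair of arms named. "One-way analysis of variance will be used for testing differences between changes in the three diet groups". A repeated-measures general linear model "will be performed in order to compare the effects of the three different treatments".
- **Threshold.** The same section sets p < 0.05 as the criterion for significance and gives no order or hierarchy of tests.

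**The concern.** The question and the sample size are about MBD against PVD. The test that carries the primary outcome's name compares each arm only with its own past. A paired test in one arm responds to anything that moves all arms together, such as being in a study, season, or a shift in the assay between Time 0 and Time 1. It cannot separate these from diet. A significant result in PVD beside a non-significant one in MBD does not show that the two diets differ.

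The between-group methods listed next can answer the question. But the text gives none of them authority over the paired tests, or over one another, and none is expressly the MBD versus PVD contrast. If the paired tests and the between-group tests disagree, the text does not say which one is the trial's result. What is at stake is the headline conclusion. A diet effect could be claimed from within-arm p values, or the deciding test could be chosen after the results are known.

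**Working it through.** **Inputs from the article.** n = 50 per arm, three arms, p < 0.05, powered difference 25% of baseline between MBD and PVD, power 80%. The SD of the change is not stated. Two-sided tests are assumed.

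**Assumptions.** Changes are normal with equal SD in each arm and the arms are independent. There is no diet difference: every arm has the same mean change, δ SDs of change. The values of δ are illustrative, since the documents give none.

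**Step 1: the plan's own figure.** n = 50 cannot be reproduced without an SD, but it can be inverted. For two independent means, n = 2·SD²·(1.960 + 0.842)² / 25². Setting n = 50 gives SD = 25 / (√(2/50) × 2.802) = 44.6% of baseline. So 50 per arm fits a between-arm comparison of change if the SD of change is about 44.6% of baseline.

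**Step 2: paired tests, no diet difference, no drift (δ = 0).**
- At least one of three significant: 1 − 0.95³ = 0.143.
- MBD and PVD discordant (exactly one significant): 2 × 0.05 × 0.95 = 0.095.

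**Step 3: the same with a common drift.** The probability p that one paired test is significant comes from the noncentral t distribution with 49 degrees of freedom, noncentrality δ√50 and critical value 2.010. Discordance between MBD and PVD is 2p(1 − p). At least one of three significant is 1 − (1 − p)³.

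| Common drift δ (SD of change) | p, one arm | MBD/PVD discordant | At least one of three |
|---|---|---|---|
| 0 | 0.050 | 0.095 | 0.143 |
| 0.1 | 0.107 | 0.190 | 0.287 |
| 0.2 | 0.284 | 0.406 | 0.632 |
| 0.283 | 0.501 | 0.500 | 0.876 |
| 0.3 | 0.548 | 0.496 | 0.907 |
| 0.5 | 0.934 | 0.124 | about 1.00 |

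Example at δ = 0.2: the noncentrality is 0.2 × 7.071 = 1.414, p = 0.284, and 2 × 0.284 × 0.716 = 0.406. Discordance cannot exceed 0.5, which it reaches at p = 0.5, near δ = 0.28. Beyond that it falls because both arms become significant together; in simulation it is about 3% at δ = 0.6.

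**Step 4: the between-group tests already in the plan, same null.** In 20,000 simulated trials at each of eight drifts from 0 to 0.6 SD, the one-way ANOVA on change rejected in 4.7% to 5.2% of trials, and so did the MBD versus PVD t test on change. A shared drift cancels in the difference between arms.

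**The case against.** The strongest reply is that a valid comparison of diets is already written in. The sentences after the paired tests plan independent t tests on change, an ANOVA and a repeated-measures model. The section opens by speaking of outcomes generally, so these cover the primary outcome. The paired tests have a narrow stated purpose, which is whether each arm changed, and nothing says that a diet effect will be concluded from them. This stands. A reader might infer that the paired test is the whole primary analysis, or that the trial has no test able to show a diet difference. The article does not support either reading.

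Three further limits also stand:

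- A reader might take 41% or 50% as the trial's false-positive rate. Those figures depend on an assumed drift at or near the peak of the curve, and they become false claims only if someone reads discordant within-arm results as a diet difference.
- Regression to the mean is not a good argument here. Participants are not selected on genotoxicity, so no shift in the arm means is expected from it.
- Season may partly cancel over a year of recruitment, and the article does not say whether Time 0 and Time 1 samples are assayed in separate batches. These are possible sources of drift and have not been shown to operate.

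It can also be said that ranking tests is commonly left to a full protocol or SAP that is not shown. That would answer a complaint about missing detail only. The article does assign a method to the primary outcome by name, and that method does not answer the stated aim or match the powered contrast. If a SAP names another primary test, this sentence would still need correcting.

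**Conclusion.** The point holds in a limited form. The article attaches to the primary outcome a test that cannot answer the trial's question. It lists several between-group methods without making one decisive, and ties none to the MBD versus PVD contrast that sets the sample size.

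The size that needs no drift assumption is about 14% for at least one significant paired test among three, and about 10% for discordant MBD and PVD verdicts, when the diets do not differ. Over assumed common drifts of 0.1 to 0.5 SD of change, discordance runs from about 12% to 50% and is not monotone. All these figures assume 50 per arm with normal, independent changes. They measure how often within-arm results would mislead someone who used them to compare diets. They are not the error rate of the between-group tests, which stay near 5%.

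**What to change.** Name one primary analysis: the MBD versus PVD difference in genotoxicity change from Time 0 to Time 1, estimated by ANCOVA with adjustment for the Time 0 value, in the intention-to-treat population, two-sided at 0.05, with the estimate and 95% CI.

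This keeps the stated metric. With the Time 0 value as a covariate, modelling the change or the Time 1 value gives the same estimated difference between arms. An unadjusted comparison of Time 1 values alone would conflict with the change metric.

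Label the three-group ANOVA, the repeated-measures model and the other pairwise comparisons as secondary. Report within-arm changes descriptively, and state that no conclusion about diets will be drawn from within-arm significance.

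The cost is wording in the statistical section or the SAP. No new data are needed and the planned 50 per arm is unchanged.

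### The named between-diet tests on change do not commit to Time 0 genotoxicity as a covariate, and they sit beside a geometric-mean model on a different scale with none named as primary

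*Protocol article*

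**What the plan says.** All references are to the protocol article.

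- **Statistical analysis, between-diet tests.** Each participant's absolute change goes into independent-sample t tests. For the three arms together, "One-way analysis of variance will be used for testing differences between changes in the three diet groups". Neither test has a covariate.
- **Statistical analysis, linear model.** A repeated-measures general linear model is also to compare the three diets, and "Data for the general linear model will be reported as geometric means with their standard errors". A further sentence announces a model adjusted for several confounders but does not list them.
- **Interventions and participant timeline.** There are two evaluations, Time 0 and Time 1.
- **Outcome measures.** The genotoxicity index is the percentage of DNA in the comet tail. The metric, for primary and secondary outcomes alike, is change from Time 0 to Time 1.
- **Sample size and power calculation.** The planning effect is a change "of 25% from baseline, between the MBD and the PVD interventions". The section gives "a sample size of at least 50 in each group of the study" and "statistical power of 80% (beta) and alpha = 0.05, totaling 150 individuals".

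No section says which between-diet analysis is primary.

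**The concern.** Two things are at stake.

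The first is efficiency. Genotoxicity is measured at Time 0 in everyone. Subtracting it fixes its coefficient at one; fitting it as a covariate lets the data choose the coefficient. Where the two readings are imperfectly correlated, subtraction usually leaves avoidable noise in the diet comparison. The repeated-measures model looks as if it might repair this, but with two visits it does not.

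The second is coherence. The planning effect is a percentage, the t tests and ANOVA work in absolute percentage points of tail DNA, and geometric means imply a log scale on which effects are ratios. A participant with twice the baseline has twice the absolute change for the same relative effect, so the scales can rank the diets differently or give different p values when baselines vary. With no primary analysis named, the plan does not say which result would carry the conclusion.

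**Working it through.** **Inputs.** From the article: 50 per arm, 80% power, alpha 0.05, 25% planning effect, two time points. Not in the article: the SD of the outcome or of its change, the sidedness of the test, and the Time 0 to Time 1 correlation rho. I assume a two-sided test, equal variances at the two times, and rho between 0.3 and 0.9.

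**1. The plan's own figure.** The 50 per arm cannot be reproduced forward, because the section refers to an earlier trial and gives no SD. Solving backward:

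- standardized difference d = sqrt(2/50) × (1.960 + 0.842) = 0.2 × 2.802 = 0.560 (0.566 with the t distribution);
- if the 25% is a between-arm difference expressed in percent of baseline, the implied SD of change is 25/0.560 = 44.6% of baseline (50.3% if the test is one-sided).

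The comparison below needs only the stated 80%, not this SD.

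**2. The repeated-measures model.** With two visits, the group-by-time term compares mean Time 1 minus Time 0 differences between arms, against the within-arm variance of those differences. That is the one-way ANOVA on change. A check on simulated data with three arms of 50 gave F = 2.6463 for both. If the model is fitted to logs, it is the ANOVA on log change. Either way, it does not use Time 0 as a covariate.

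**3. Variance ratio.** With common variance s²:

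- change score: 2s²(1 − rho);
- ANCOVA residual: s²(1 − rho²);
- ratio ANCOVA/change = (1 − rho²) / [2(1 − rho)] = (1 + rho)/2.

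**4. Power with 50 per arm.** If the change-score test has 80% power, ANCOVA power is Φ(2.802 / sqrt((1 + rho)/2) − 1.960). The n per arm that would keep 80% is 50 × (1 + rho)/2, rounded up. The last column reverses the calibration: if the 50 had been derived for ANCOVA, it gives the power left for the change-score test.

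| rho (assumed) | variance ratio | ANCOVA power | n per arm for 80% | change-score power if 50 suits ANCOVA |
|---|---|---|---|---|
| 0.3 | 0.65 | 93.5% | 33 | 61.7% |
| 0.5 | 0.75 | 89.9% | 38 | 67.9% |
| 0.7 | 0.85 | 86.0% | 43 | 73.3% |
| 0.9 | 0.95 | 82.0% | 48 | 78.0% |

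**5. The scales side by side.** Absolute-change tests estimate a difference in tail-DNA points. A log-scale model estimates a ratio. The 25% can be read either way: as 25% of the baseline mean it is an absolute quantity, and as a relative effect it matches only the log-scale model. Even as a ratio it needs a direction. MBD 25% above PVD is a ratio of 1.25 (log 0.223); PVD 25% below MBD is 1/0.75 = 1.33 (log 0.288). At equal log-scale SD, these need sample sizes that differ by (0.288/0.223)² ≈ 1.7.

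**The case against.** The strongest defense has three parts.

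- **Change from baseline is a legitimate choice.** It matches the declared outcome metric, and under randomization the test is valid. This stands. A reader might infer that the estimates are biased by baseline imbalance. They are not: averaged over randomizations the contrast is unbiased, and a shift arises only conditional on a chance imbalance, in either direction. The point concerns efficiency.
- **A confounder-adjusted model is announced, and an article may leave its covariate list to the full protocol.** This stands in part. It cannot be said that the whole plan lacks baseline adjustment. But an unnamed list does not commit to Time 0 genotoxicity, and the article itself states the less efficient tests explicitly.
- **The gain may be small.** At rho 0.9 it is two percentage points of power, and under the first calibration the planned test keeps its 80%. Both are true. The gain is still free, and it is substantial at lower correlations.

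Three further readings go beyond the text:

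- **That the 25% effect is never tested.** It is a planning value, the MBD–PVD difference in change is tested, and a log-scale model would estimate a relative effect.
- **That geometric means are impossible because changes can be negative.** The sentence concerns the data for the linear model, which can be the non-negative Time 0 and Time 1 levels.
- **That the diets will be compared through the group main effect of the repeated-measures model, which would average in the pre-diet value.** The article does not name that term, so power figures for it would rest on supposition.

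**Conclusion.** The concern holds as a matter of efficiency and clarity. None of the named between-diet tests commits to Time 0 genotoxicity as a covariate, and the two-visit repeated-measures model adds no such adjustment. Moving to ANCOVA would raise a true 80% to between about 94% (rho 0.3) and 82% (rho 0.9) with the same 50 per arm.

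That size rests on equal variances, a two-sided test, the 80% applying to the change score, and a correlation the article does not give. The direction is less fragile: in large samples ANCOVA is no less efficient than the change score, and it gains nothing only if the Time 1 on Time 0 slope equals one.

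Separately, absolute change and geometric means answer different questions, only the latter matches a relative reading of the 25%, and nothing is named as primary. This does not invalidate the trial, but it should be settled before the data are analyzed.

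**What to change.** - Name one primary between-diet analysis: ANCOVA of Time 1 genotoxicity on diet and Time 0 genotoxicity, with the MBD–PVD contrast.
- Fix the scale in advance. If geometric means are to be reported, fit both readings as logs and give the MBD/PVD ratio with a 95% confidence interval back-transformed from the log scale.
- State the 25% planning effect on that scale, including its direction, with the SD that goes with it.
- Keep the change-score tests and the repeated-measures model as supportive analyses at most.
- Use the same form for the continuous secondary outcomes.

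The cost is mostly wording, since Time 0 is already collected. Two small items remain. Near-zero comet readings need a rule set in advance if logs are used. Restating the planning effect as a ratio also needs a log-scale SD, which the article does not give and the sponsor would have to supply.
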